#### Data Collection and Management

Data are recorded in an eCRF developed using Clinsight (Ennov Inc). The eCRF is used for data entry at each investigator site, and every center is responsible for patient anonymization. The eCRF was created, tested, and validated before the start of data entry. The data necessary for monitoring the primary and secondary endpoints are identified and managed at regular intervals throughout the trial. Data are monitored by the data management team of the data management department of University Hospital of Lille using predefined data management rules, and queries are automatically edited. Finally, overall automated monitoring is performed by the data manager at the end of data entry. In case of discrepancies, queries are edited to resolve the problems encountered. After validation, the database is frozen and exported for analysis.

### Statistical Analysis

#### Overview

Statistical analysis will be conducted in a blinded fashion with a blinded code for the intervention. All statistical analyses will be carried out independently in the Department of Biostatistics of the University Hospital of Lille. SAS 9.3 (SAS Institute Inc) software or later will be used. *P* values will be reported as the actual values, unless *P*<.001. No interim analyses are planned. A detailed statistical analysis plan (SAP) will be drafted and validated before the database is frozen. Patient characteristics at baseline will be described for each of the 3 arms; the quantitative variables will be described either by the mean and standard deviation in case of a Gaussian distribution or by the median and interquartile range if not. The normality of the distributions will be verified graphically by histograms and by the Shapiro-Wilk test. The qualitative variables will be described by the numbers and percentages of each category. All analyses for the primary and secondary objectives will be performed on all randomized patients in their original group of randomization according to intention-to-treat (ITT) principles. No subgroup analysis will be performed.

#### Main Objective

Comparison of the primary endpoint (2-month change in STAI scale) between each experimental group and the control group will be performed separately using an analysis of covariance with an adjustment for the STAI baseline value and the center. Since 2 comparisons will be made for the primary analysis, each of them will be performed at the 2.5% significance level (Bonferroni correction). The absolute mean differences and effect sizes (standardized mean difference) will be reported with the 95% confidence interval. In case of deviation from normality of model residuals, nonparametric analysis will be used; absolute changes between baseline and 2-month visits will be calculated and compared between the experimental arm and control arm using nonparametric analysis of covariance adjusted for baseline values [63,64]. The primary analysis will be conducted according to the ITT principle. Missing values will be handled by multiple imputation procedures. Missing data will be imputed under the missing at random assumption using a regression switching approach (chained equation with m=20 imputations) with predictive mean matching method for continuous variables and logistic regression (binary, ordinal, or polynomial) for qualitative variables [65]. The imputation procedure will be performed using the main baseline characteristics, outcome, and variable group of randomization, and multiple imputed data sets will be combined using Rubin’s rules [66,67]. Sensitivity analyses will first be conducted using all available STAI measurements (complete cases analysis) and second in patients without major deviation from protocol (per protocol analysis); major deviations will be specified in the SAP.

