#### Recruitment

The study is being conducted at 3 university hospitals (Lille, Amiens, Caen) in the northwest area of France as part of the university communities (*InterRégional*). Patients are referred by their general practitioner to a psychiatric consultation service for psychological treatment of anxiety symptoms in a context of recent stress. To improve recruitment, general practitioners in the 3 areas were informed of the study by a local investigator during continuing medical education, during scientific meetings, and through all types of collaborative contacts between primary care and psychiatry services. We also directly informed the general practitioners who were involved in previous research on ADA and CBT and invited them to refer patients.

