#### Randomization

Immediately after inclusion and assessment, patients are randomly allocated in a 1:1:1 ratio into 3 groups using a Web-based central randomization: patients using a digital stress management module (group 1), patients following the stress management module guided by a therapist in attendance (group 2), and patients on a waiting list and benefiting from usual care through their attending physician (group 3).

The randomization sequence is provided by an independent statistician (who does not take part in assessing the patients at any point in the study) using computer-generated random numbers with block sizes of 6 and center stratification consistent with the Consolidated Standards of Reporting Trials (CONSORT) [48]. The randomization sequence is implemented in the electronic case report form (eCRF) system to ensure a centralized, real-time randomization procedure.

A document describing the randomization procedure is kept confidential in the Clinical Investigation Centre of Lille University Hospital.

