#### Sample Size

In a study on the clinical and psychometric characteristics of ADA, the mean (standard deviation) of the STAI baseline score was 52.1 (SD 14.6) [4]. Two clinical studies with patients with generalized anxiety disorder, 1 comparing CBT with relaxation [61] and the other comparing CBT with brief psychodynamic psychotherapy [62], showed changes in the STAI-T scores of 7 and 16, respectively. In view of these results, we hypothesize that an average difference between each experimental arm and the control arm of 11.5 (the mean of 7 and 16). To demonstrate this difference in variation with a standard deviation of the STAI score change of 14.6 (assuming a conservative correlation coefficient of 0.5 between the baseline and 2-month STAI measures), a 2.5% type I error (using a Bonferroni correction for the 2 prespecified comparisons), and a power of 80%, it is necessary to include 32 patients per group. Although analysis of the primary outcome will be adjusted for baseline values, the sample size calculation does not take into account this adjustment to maximize the power. Finally, considering 20% ​​missing data, 120 patients (40 per group) are planned in this clinical trial.

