#### Secondary Objectives

For the secondary endpoints of the HADS anxiety subscale, PSWQ, VAS-stress, PSS, BDI, and HADS depression subscale scores, comparisons of the changes between the baseline and the 2-month visit between each experimental group and the control group will be performed separately with the same methodology used for the primary endpoint.

Comparison of the change between the baseline and the 6-month visit for the primary endpoint and secondary endpoints between each experimental group and the control group will be performed separately using a linear mixed model. In this model, we will include the 2 measurements (at 2 and 6 months) for the time effect, the group effect (experimental/control), an adjustment for baseline values and center, and a time × group interaction. A contrast with a 2.5% type I error will be used to compare the 6-month change between the experimental and the control group.

The efficacy of the 2 therapeutic programs (face-to-face versus digital support) at 2 and 6 months will be compared using an analysis of covariance at the 5% significance level to compare the variations in the STAI score between the groups, adjusting for the baseline value.

VAS satisfaction and consumption of tobacco, alcohol, and drug use will be analyzed in each group using descriptive statistics.

The full version of the protocol can be viewed in Multimedia Appendix 4.

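### The digital versus face-to-face ANCOVA leaves out center, although randomization is stratified by center and the parametric program-versus-control models adjust for it

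*Protocol article*

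**What the plan says.** The protocol article lists the covariates model by model.

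- **Randomization:** the sequence is generated "using computer-generated random numbers with block sizes of 6 and center stratification", with three hospitals and 1:1:1 allocation.
- **Main Objective:** the 2-month STAI change is compared between each program and control; these comparisons "will be performed separately using an analysis of covariance with an adjustment for the STAI baseline value and the center". Each is tested at 2.5%.
- **Secondary Objectives, other 2-month endpoints, program versus control:** the same method as for the primary endpoint, hence again with center.
- **Secondary Objectives, 6 months, program versus control:** a linear mixed model that contains "the group effect (experimental/control), an adjustment for baseline values and center, and a time × group interaction".
- **Secondary Objectives, program versus program:** at 2 and 6 months the two programs "will be compared using an analysis of covariance at the 5% significance level", and the stated purpose and covariates are "to compare the variations in the STAI score between the groups, adjusting for the baseline value". Center is not named.

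**The concern.** Stratifying by center balances the arms within each hospital. That balance reduces the true variability of the estimated difference, but the reported standard error reflects the reduction only if center is in the model. Without it, differences between hospitals in mean STAI change stay in the residual variance. The interval is then wider than the design warrants and the test rejects less often than its nominal level.

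The comparison affected is one that readers will look at. Under Hypotheses the two programs are expected to be equally effective, and under Choice of Comparators the face-to-face arm is there to show the value of eLearning. An unduly wide interval makes a non-significant result slightly more likely, and under that hypothesis such a result is easily misread as support. There is no evident reason for this comparison to have less adjustment than the others.

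**Working it through.** **Inputs from the Sample Size section.** Difference 11.5 points, SD of change 14.6, baseline to 2-month correlation 0.5, type I error 2.5% per primary comparison (taken as two-sided), power 80%, 32 per group, 20% missing, 40 per group.

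**The plan's own figure.** n = 2(z₀.₉₈₇₅ + z₀.₈₀)² × SD² / Δ² = 2 × (2.241 + 0.842)² × 14.6² / 11.5² = 2 × 9.505 × 1.612 = 30.6, so 31 by the normal approximation. With the noncentral t, power is 78.7% at 31 and 80.1% at 32. So 32 is reproduced, and 32 / 0.8 = 40.

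**Residual SD after baseline adjustment.** With r = 0.5 and equal variances, the SD at each visit is also 14.6, and the ANCOVA residual SD is 14.6 × √(1 − 0.5²) = 12.64 (variance 159.9).

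**Effect of omitting center.** Assume that center means vary with SD σc, and that the three hospitals recruit 1/2, 1/4 and 1/4 of patients. The documents give neither figure. The expected variance that center adds to the residual is σc² × (1 − 1/4 − 1/16 − 1/16) = 0.625σc². Stratification keeps the arms balanced within centers, so the true error of the difference hardly changes while the reported standard error is multiplied by √(1 + 0.625σc² / 159.9). The true type I error is then about 2 × [1 − Φ(1.96 × that factor)].

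| Assumed center SD | Added variance | SE factor | Approx. type I error at nominal 5% |
|---|---|---|---|
| 0 | 0 | 1.000 | 5.0% |
| 3 | 5.6 | 1.017 | 4.6% |
| 6 | 22.5 | 1.068 | 3.6% |

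**Check by simulation** (32 per arm, stratified blocks, 3000 trials per scenario). Mean standard error of the program-versus-program difference and mean 95% half-width:

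| Assumed center SD | SE without center | SE with center | Half-width without | Half-width with |
|---|---|---|---|---|
| 0 | 3.173 | 3.174 | 6.35 | 6.35 |
| 3 | 3.225 | 3.171 | 6.45 | 6.35 |
| 6 | 3.385 | 3.168 | 6.77 | 6.34 |

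The ratios are 3.225 / 3.171 = 1.017 and 3.385 / 3.168 = 1.068, as in the formula. A longer run of the two-arm comparison (40,000 trials, same settings) put the type I error without center at 4.4% (SD 3) and 3.8% (SD 6), and with center at 4.9% and 5.0%. At 40 per arm and SD 3 the standard error ratio is 2.888 / 2.836 = 1.018, so the proportional loss does not depend on dropout.

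**Cost of adding center.** Two program arms of 32 give 64 patients. Residual degrees of freedom fall from 64 − 3 = 61 to 64 − 5 = 59, and the 5% critical value moves from 2.000 to 2.001.

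**Whether a three-arm model is needed.** At 32 per arm, one ANCOVA on all three arms has 96 − 6 = 90 residual degrees of freedom against 59. At the 2.5% level the critical value is 2.280 against 2.300, so intervals are about 0.9% narrower. Power for 11.5 points is 91.1% against 90.6%. This assumes equal residual variances. If the control SD is 0.7 of that in the program arms, the pooled model gives a program-versus-control half-width of 6.58 against 6.30 from the two-arm fit. It also understates the program-versus-program standard error (2.89 against a simulated true value of 3.10).

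**The case against.** The strongest case against the point is that it is small and may be only abbreviation. It concerns a secondary comparison. The consequence is a slightly conservative test, not a false positive. The size rests on a center SD that the documents do not give. The article also condenses a full protocol that is not shown, and the nonparametric fallback under Main Objective likewise mentions baseline alone, so covariate lists may simply have been shortened.

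Most of this stands, and it sets the grade. It does not remove the point. The article states covariates for each parametric model, and the list for this one differs from the others. Followed as written, it leaves out the stratification factor.

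A reader might go further and infer that fitting each pair of arms separately is itself a fault, because one three-arm model would be more precise and would make the three reported differences add up. The documents do not support that. The separate ANCOVAs are valid, keep the Bonferroni control, and match the pairwise sample size calculation, which uses "a 2.5% type I error (using a Bonferroni correction for the 2 prespecified comparisons), and a power of 80"%. The gain from pooling is about half a power point and can reverse when arm variances differ. The failure of the three estimates to add up has an SD of about 0.5 points, against a standard error of about 3.2, and is a matter of presentation.

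**Conclusion.** The point holds for the center term only. As written, the digital versus face-to-face ANCOVA at 2 and 6 months is out of line with the stratified randomization and with the parametric program-versus-control models. If center means vary with an SD of 3 to 6 points (assumed), its standard error is about 2% to 7% too large and the test runs at about 4% instead of 5%. If centers do not differ, nothing is lost. The calculation takes the plan's SD and correlation at 2 months and an assumed split of recruitment over hospitals; carrying it to 6 months assumes similar variability there.

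Two stronger inferences should be resisted. The omission does not bias the estimated difference between programs, because the arms are balanced within centers. Nor does it touch the primary analysis or the planned 120 patients. The point is minor: worth correcting because the correction costs almost nothing.

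**What to change.** In Secondary Objectives, add center to baseline STAI as a covariate in the digital versus face-to-face ANCOVA at both 2 and 6 months, and carry the same wording into the statistical analysis plan, which the article says will be validated before the database is frozen.

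The cost is one phrase and 2 residual degrees of freedom. No new data are needed, and neither the sample size nor the significance levels change. The primary two-arm ANCOVAs can stay as they are. If the sponsor wants all three contrasts to come from one model, a three-arm ANCOVA is an option, preferably with arm-specific residual variances, but it is not required.

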### Hypotheses

We hypothesize that (1) both therapeutic programs will have a greater clinical impact on the reduction of anxiety symptoms, perceived stress, and depressive symptoms compared with a WLC in the short term (2 months), and this effect will be maintained in the long term (6 months); (2) the 2 therapeutic programs will have the same effectiveness in reducing these symptoms; (3) both therapies will be more cost effective than will WLC; (4) these 2 programs both reduce the consumption of tobacco, alcohol, and drugs compared with WLC; and (5) participants will be satisfied with the 2 therapeutic programs.

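### Holm's step-down test would recover power that plain Bonferroni gives up in the two primary comparisons, at the same 5% familywise error and with no extra patients

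*Protocol article*

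**What the plan says.** The Main Objective section of the statistical analysis compares the 2-month STAI change "between each experimental group and the control group will be performed separately using an analysis of covariance", adjusted for baseline STAI and center. On multiplicity it fixes a flat split: "Since 2 comparisons will be made for the primary analysis, each of them will be performed at the 2.5% significance level (Bonferroni correction"). It mentions no step-down. Effect estimates "will be reported with the 95% confidence interval".

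The Sample Size section uses the same level and plans for "an average difference between each experimental arm and the control arm of 11.5 (the mean of 7 and 16"), with an SD of change of 14.6. It concludes that for "a power of 80%, it is necessary to include 32 patients per group". Allowing for 20% missing data brings this to 40 per group and 120 in total. The section says that the calculation leaves out the gain from baseline adjustment.

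The first item under Hypotheses is that "both therapeutic programs will have a greater clinical impact on the reduction of anxiety symptoms" than the wait list. The Discussion likewise gives the aim as demonstrating the efficacy of two programs. No section gives a power for showing both.

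**The concern.** Under the plan each comparison stays at 2.5% even after the other has been rejected. At that point only one null hypothesis can still be true, so the remaining comparison could be tested at the full 5% without breaching the familywise bound. Plain Bonferroni leaves that half of the error rate unused.

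The loss falls on the weaker of two effective programs, and so on the claim that both work, which is how the first hypothesis is worded. The trial is small (32 evaluable per arm). The Digital Stress Management section of the Introduction also reports a pooled anxiety effect for computer- and Internet-based programs that is well below the effect planned here. The digital arm may therefore be the one that needs the second step.

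**Working it through.** **Inputs.** From Sample Size: difference 11.5, SD of change 14.6, correlation 0.5, level 2.5% per comparison, power 80%, 32 evaluable per group. From Randomization: 1:1:1, so both comparisons share one control arm and the test statistics correlate at about 0.5. From Digital Stress Management: anxiety effect d = 0.32, 95% CI 0.17 to 0.47. Assumed: two-sided tests (sidedness is not stated; a two-sided 2.5% test reproduces the 32), equal SDs and normal data.

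**Step 1: reproduce the plan's figure.**
- Normal approximation: n = 2 × [14.6 × (2.241 + 0.842) / 11.5]² = 30.64, so 31 per group.
- t test: standard error = 14.6 × √(2/32) = 3.65; noncentrality = 11.5 / 3.65 = 3.15. Power is 78.7% at n = 31 and 80.1% at n = 32, so 32 reproduces.
- 32 / (1 − 0.20) = 40 per group; 40 × 3 = 120.

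**Step 2: the two rules.**
- Bonferroni: reject a comparison if its P ≤ 0.025.
- Holm: reject the smaller P if ≤ 0.025; if so, reject the larger P if ≤ 0.05.

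The first step is identical, so the chance of at least one rejection cannot differ. Only the second comparison can gain.

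**Step 3: power at 32 per arm.** Simulation of three normal arms with a shared control and pairwise t tests, at least 400,000 trials per row.

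| Scenario | Quantity | Bonferroni | Holm |
|---|---|---|---|
| 11.5 in both arms, SD 14.6 | each program | 80.1% | 84.9% |
| | both programs | 68.9% | 78.4% |
| | at least one | 91.4% | 91.4% |
| 11.5 in both arms, SD 12.64 | each program | 90.7% | 93.7% |
| | both programs | 84.3% | 90.4% |
| | at least one | 97.1% | 97.1% |
| Face-to-face 11.5, digital 6.86 | digital | 34% | 44% |
| Face-to-face 11.5, digital 4.67 | digital | 16% | 24% |

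Check on the first block: at least one = 2 × each − both. Bonferroni: 2 × 80.1 − 68.9 = 91.3. Holm: 2 × 84.9 − 78.4 = 91.4. Both agree within rounding.

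The SD of 12.64 is the residual SD after baseline adjustment at the stated correlation: 14.6 × √(1 − 0.5²) = 12.64. It approximates the planned analysis of covariance, ignoring center.

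The digital effects are 0.47 × 14.6 = 6.86, at the upper confidence limit of the pooled anxiety effect, and 0.32 × 14.6 = 4.67, at its point estimate. The planned effect is 11.5 / 14.6 = 0.79.

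**Step 4: error rates.**
- Neither program works: the chance of any false rejection is 4.6% under both rules.
- One program works by 11.5 points and the other not at all: false rejection for the ineffective one is 2.5% under Bonferroni and 4.3% under Holm.
- One program has a very large effect (50 points) and the other none: 2.5% and 5.0%. This is the worst case, and it meets the 5% bound.

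**The case against.** The strongest reply is that nothing here is wrong. Bonferroni controls the familywise error, the 2.5% level runs consistently through the sample size, the primary analysis and the 6-month contrast, and the sample size reproduces. All of that stands. This is a point of efficiency only.

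Three stronger readings are tempting, and the document does not support them.
- A reader might infer that the stated 80% power is overstated, because the chance of showing both programs is 69%. The Sample Size section claims 80% for each arm against control. The primary comparisons are run separately, and nowhere does a positive trial depend on both succeeding.
- A reader might take 69% as the power of the planned analysis. It belongs to unadjusted t tests. The plan adjusts for baseline, and at its own correlation of 0.5 plain Bonferroni already gives about 84% for both.
- A reader might infer that Holm rescues the digital arm. At the pooled estimate of d = 0.32 its power reaches only 24%. That estimate is also described as relative to other types of interventions, not to a wait list, and the Hypotheses section expects the two programs to be equally effective.

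It can also be said that the extra power is paid for in error: an ineffective program runs up to twice the false-positive risk when the other works. That is true, but the risk stays within the 5% familywise rate that the plan accepts. Bonferroni's simple matching intervals are a weak defense here, because the article plans 95% intervals, which do not correspond to its 2.5% tests in any case.

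**Conclusion.** The point holds as a modest, inexpensive gain. Holm is at least as powerful as the planned rule in every scenario and keeps strong 5% control under any correlation. The gain is about 5 percentage points per program and 9.5 for both on the unadjusted assumptions, about 3 and 6 with baseline adjustment at r = 0.5, and about 8 to 10 for a weaker digital arm beside an effective face-to-face arm. It is zero for showing at least one program.

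The figures rest on two-sided tests, equal SDs, normal data, 32 evaluable per arm and no center effect. The direction of the gain does not depend on these; its size does. Priority is low: the plan is valid as it stands.

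**What to change.** State in the statistical analysis plan, which the article says will be validated before the database is frozen, that the two primary comparisons are tested with the Holm procedure at a two-sided familywise 5% and reported with Holm-adjusted P values. In the same place, say whether the 2.5% level in the Secondary Objectives section stays as it is. That section carries the primary method to six secondary scales at 2 months and fixes a 2.5% contrast at 6 months, so changing the primary rule alone would leave this unclear.

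If simultaneous 97.5% intervals are added to the planned 95% ones, note that a second-step rejection can go with a 97.5% interval that includes zero. If a power for showing both programs is given, label 69% and 78% as based on unadjusted tests; they should not stand as the power of the planned analysis of covariance.

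The cost is a few sentences and no patients. Because 50 of 120 participants had been enrolled at the time of writing, the change alters a published testing rule during an open-label trial, so it should be dated and recorded as made before the freeze.

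### The two primary comparisons are tested at 2.5% but reported with 95% confidence intervals not labelled as unadjusted, so an interval can exclude zero beside a failed test (minor, reporting only)

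*Protocol article*

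**What the plan says.** Under Main Objective, the protocol article explains the error level with "Since 2 comparisons will be made for the primary analysis" and continues that "each of them will be performed at the 2.5% significance level (Bonferroni correction"). The next sentence fixes the interval level: "The absolute mean differences and effect sizes (standardized mean difference) will be reported with the 95% confidence interval".

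Sample Size uses the same level: "a 2.5% type I error (using a Bonferroni correction for the 2 prespecified comparisons), and a power of 80"%.

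Secondary Objectives applies the primary method to the 2-month changes in the other scales, so those comparisons take over both the 2.5% test and the 95% interval. For 6 months it says "A contrast with a 2.5% type I error will be used to compare the 6-month change" and names no interval level. It names none for the comparison of the two programs either, which is tested at 5%.

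Nowhere does the article give a 97.5% or multiplicity-adjusted interval, or say that the 95% intervals are unadjusted or descriptive.

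**The concern.** A two-sided test at level α and a 100(1 − α)% interval from the same model give the same verdict on zero. At 2.5% the matching interval is 97.5%. With 95% intervals there is a band of results, P from .025 to .05, where the interval excludes zero and the prespecified test has failed.

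Two active arms share one control, so a split outcome is realistic: one program passes, and the other ends at, say, P = .03 with an interval clear of zero. Many readers take the interval as the verdict and would credit the second program with an effect that the plan's own rule does not grant. What is at stake is how the primary result is presented and read.

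**Working it through.** **Inputs** (protocol article, Sample Size and Main Objective): difference 11.5 points; SD of change 14.6, which agrees with a baseline SD of 14.6 and a correlation of 0.5, since √(2 × 14.6² × (1 − 0.5)) = 14.6; level 2.5% per comparison; power 80%; 32 per group, or 40 after allowing for 20% missing data; analysis of covariance adjusted for baseline.

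**1. Is the 2.5% one-sided or two-sided?** The article does not say. A one-sided 2.5% test would pair correctly with a two-sided 95% interval, so this has to be settled first. The normal approximation is n = 2(SD/difference)²(z_α + z_power)² per group, with 2(14.6/11.5)² = 3.22.
- Two-sided 2.5%: 3.22 × (2.241 + 0.842)² = 30.6, so 31. The noncentral t calculation gives 32 (power 80.1% at 32, 78.7% at 31).
- One-sided 2.5%: 3.22 × (1.960 + 0.842)² = 25.3, so 26.

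The article's figure ("it is necessary to include 32 patients per group") is reproduced only by the two-sided level. Then 32/0.80 = 40, and 3 × 40 = 120, as stated. The level is also described as Bonferroni for two comparisons, that is 5%/2.

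**2. Width and discordant zone.** Half-width = t × SE, with SE = 14.6 × √(2/n).

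| Per group | SE | df | 95% half-width | 97.5% half-width | Ratio |
|---|---|---|---|---|---|
| 32 | 3.65 | 62 | 7.30 | 8.38 | 1.149 |
| 40 | 3.26 | 78 | 6.50 | 7.46 | 1.148 |

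An observed difference between the two half-widths gives an interval that excludes zero and a test that fails. Baseline adjustment shortens both intervals and leaves the ratio almost unchanged.

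**3. Familywise error if the intervals were read as tests.** With equal groups and a shared control, the two estimates have correlation (σ²/n)/(2σ²/n) = 0.5. For a bivariate normal under the global null, 1 − P(both |Z| < c) is
- 9.1% at c = 1.960 (95% intervals), and at most 10% by the Bonferroni bound;
- 4.6% at c = 2.241 (the planned tests), and at most 5%.

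**4. How often would it happen?** With the article's correlation of 0.5, the residual SD of the baseline-adjusted analysis is 14.6 × √(1 − 0.5²) = 12.64. At a true difference of 11.5, P falls between .025 and .05 with probability 4.1% per comparison (32 per group) or 1.9% (40 per group). Simulating three arms with a shared control gives, for at least one of the two comparisons:

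| True difference, both programs | 32 per group | 40 per group |
|---|---|---|
| 11.5 | about 8% | about 4% |
| 7 to 8 | about 20% to 22% | about 17% to 21% |

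The lower range is relevant because the planned value is "an average difference between each experimental arm and the control arm of 11.5 (the mean of 7 and 16"), so one of its two source values is itself 7.

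**The case against.** The decision rule is explicit. The tests run at 2.5%, the trial is sized on that level, and the Overview of the statistical analysis promises actual P values, so P = .03 would be printed against a known threshold. Unadjusted 95% intervals beside adjusted tests are common and defensible. A detailed SAP is announced and could settle the labelling. Most of this stands, and it is why the point is minor. It does not remove the point, because the article positively fixes 95% in the sentence after the 2.5% rule and does not label the intervals.

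Four stronger readings are tempting, and the document does not support them.
- **The intervals are wrong or too narrow.** Each 95% interval keeps its own nominal coverage, and the article claims no simultaneous coverage.
- **The type I error is inflated.** The 9.1% arises only if a reader sets the stated test aside and uses the intervals instead.
- **The 6-month contrast has the same mismatch.** No interval level is stated there, so there is nothing to contradict.
- **Discordance is frequent at the planned effect.** An unadjusted t test with 32 per group would give about 14% at 11.5 points, but the planned analysis adjusts for baseline, which brings this to about 4% to 8%.

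**Conclusion.** The mismatch is real and minor: it affects reporting and interpretation only. It covers the two primary comparisons and the 2-month secondary comparisons that inherit their method. The frequency of a discordant primary result is modest if the planned effect is true, and roughly one trial in five or six if the effect is 7 to 8 points.

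These frequencies assume normal data, an SD of 14.6, a baseline correlation of 0.5, the same true effect for both programs, and 32 to 40 analyzed per group. They leave out the center adjustment and multiple imputation. They also count trials in which the other program clearly succeeds. The existence of the mismatch depends on none of this. It rests only on the 2.5% level being two-sided, which the article does not state in words but its sample size implies.

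**What to change.** Under Main Objective, replace 95% by 97.5% for the mean differences and standardized mean differences of the two primary comparisons. Let the 2-month secondary comparisons follow. If intervals are given for the 6-month contrasts tested at 2.5%, use 97.5% there too.

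If 95% intervals are preferred, add one sentence saying that they are not adjusted for the two comparisons and that success is judged only by P < .025.

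Either change can go into the SAP and its table shells before the database is frozen. The first costs intervals about 15% wider, the second one sentence. The tests, the error control and the 120 patients stay as planned.
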